### Data collection and management

Quantitative outcomes will be collected through the Research Electronic Data Capture (REDCap) online platform [60]. Pharmacists and participating patients will be asked to complete two online questionnaires: one before randomization and another at the end of the 6-month follow-up. Non-responders will be reminded using email and telephone. Qualitative data will be collected at the end of the study through semi-structured interviews. These interviews will be conducted by telephone or Teams and audio-recorded. Participants’ confidential information will be managed according to best practices, stored on a secured server, and kept in password-protected documents accessible only to a limited number of research team members who have signed a confidentiality agreement.

### Progression criteria

The following indicators will be used to determine the pilot study’s acceptability and feasibility: ≥ 50% of eligible patients agreeing to participate; ≥ 70% of recruited pharmacists having completed the training and using the program tools; ≥ 75% of pharmacists and patients deeming the program acceptable and potentially beneficial. For the objective related to the program’s preliminary effects, we will consider that an effect size of ≥ 0.50 on factors hypothesized to influence adherence, such as intention, as indicating that the program has the potential to enhance AET adherence, since a moderate to large effect on such factors is likely to produce a change in the targeted behavior (i.e., AET adherence [61]).

### Sample size

We estimated that most clusters would include between 1 and 3 patients (mean = 2) and that we would be able to recruit approximately 33 pharmacies and 66 patients per group. To assess the precision of our acceptability and feasibility indicators, we calculated Wald 95% confidence intervals (CI) [62] taking into account an intra-cluster correlation (ICC) of 0.02 for patients from the same pharmacy [63]. For example, for the acceptability indicator defined by a participation rate of at least 50% of eligible patients, a sample size of 132 patients will lead to a 95% CI of 41.5% to 58.5%. For one of our main feasibility indicators, which is at least 70% of pharmacists completing the training, a sample size of 33 pharmacists will result in a 95% CI of 54.4% to 85.6%. Finally, for the indicator assessing whether at least 75% of pharmacists and patients deem the program acceptable and potentially beneficial, a sample size of 33 pharmacists and 66 patients will result in a 95% CI of 60.2% to 89.8% and 64.4% to 85.6%, respectively. This pilot study is not designed to assess the program’s efficacy on adherence [64]. However, we will be able to explore the program’s preliminary effects on factors expected to influence AET adherence. The anticipated sample size will enable us to detect moderate to large effect sizes (*d* ≥ 0.50) (mean of 2 patients per cluster; ICC = 0.02 [63]; correlation of 0.5 between baseline and 6-month follow-up [65]; power = 0.80; α = 0.05). For the qualitative phase, we will determine the final number of semi-structured interviews to be conducted for each group (pharmacists and patients) using data saturation (i.e., when no new information is provided by the interviews). From our previous work conducted among these groups [66–68], saturation may be reached after 15 to 20 interviews.

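### The planning interval for the 50% participation criterion is computed on the 132 women to be enrolled, not on the eligible women invited; the slip is conservative and minor

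*Protocol article*

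**What the plan says.** The Progression criteria section of the protocol article sets the threshold at "50% of eligible patients agreeing to participate" or more. The Sample size section uses the same definition, giving its worked example "for the acceptability indicator defined by a participation rate of at least 50% of eligible patients". Both passages make eligible patients the denominator.

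The Sample size section sets the planned size by stating that "we would be able to recruit approximately 33 pharmacies and 66 patients per group". That is 66 pharmacies and 132 women in all, a mean of 2 per pharmacy. It then says, for the participation indicator, that "a sample size of 132 patients will lead to a 95% CI of 41.5% to 58.5" percent. The intervals are described as Wald intervals, computed "taking into account an intra-cluster correlation (ICC) of 0.02 for patients from the same pharmacy".

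The Recruitment and Allocation and blinding sections fix the order of events. Pharmacy staff contact potentially eligible women, the research team verifies eligibility, and consent and the baseline questionnaire follow. Only then is the pharmacy randomized, and nobody can join the cluster afterwards. The article gives no figure for the number of eligible women expected.

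**The concern.** A participation rate is the number who agree divided by the number eligible. By the article's own sequence, the 132 women in the randomized clusters have all agreed; among them the rate is 100% by construction. Using 132 as n puts the expected numerator where the denominator belongs.

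The interval is the only statement of precision attached to the first-listed progression criterion, and recruitment rate is also an outcome for judging whether a large trial is feasible. A reader who takes the sentence at face value gets the wrong precision. The reader also gets no indication of how many eligible women must be found to enrol 132.

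A second, much smaller point concerns the same sentence: the text says the ICC was taken into account, and the printed limits do not reflect it.

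**Working it through.** **Inputs from the article.** Threshold p = 0.50 (Progression criteria; Sample size). Planned enrolment 2 × 66 = 132 women in 2 × 33 = 66 pharmacies, mean 2 per pharmacy; ICC 0.02; Wald 95% interval (all Sample size).

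**Formula.** p ± 1.96 × √[p(1 − p) × DE / n], with design effect DE = 1 + (m − 1) × ICC and m women per pharmacy.

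**Step 1: reproduce the stated interval.**
- n = 132, DE = 1: 1.96 × √(0.25/132) = 8.53 points, giving 41.47% to 58.53%. This matches the printed 41.5% to 58.5%.
- n = 132, DE = 1 + (2 − 1) × 0.02 = 1.02: 8.61 points, giving 41.39% to 58.61%, or 41.4% to 58.6% rounded.

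The denominator used is therefore 132, and the printed limits carry no design effect. For comparison, the article's other patient interval (75%, n = 66, printed as 64.4% to 85.6%) fits DE = 1.02 (64.45% to 85.55%) better than DE = 1 (64.55% to 85.45%). The adjustment appears in one patient interval and not in the other. The effect here is 0.1 point at each limit.

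**Step 2: put the eligible women in the denominator.** If 132 are enrolled at 50% participation, the eligible number is 132 / 0.50 = 264, or 264 / 66 = 4 per pharmacy on average.

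| Design effect at n = 264 | Half-width (points) | 95% interval |
|---|---|---|
| 1 (none) | 6.03 | 43.97% to 56.03% |
| 1.02 (m = 2) | 6.09 | 43.91% to 56.09% |
| 1 + (4 − 1) × 0.02 = 1.06 (m = 4) | 6.21 | 43.79% to 56.21% |

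Against the stated 8.53 points, the interval is too wide by 8.53 − 6.21 = 2.3 to 8.53 − 6.03 = 2.5 points on each side.

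**Step 3: range for the assumed rate.** The article does not state the eligible number, so it depends on the rate assumed. With 132 enrolled in 66 pharmacies:

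| Assumed rate | Eligible women | Per pharmacy | 95% interval, DE = 1 | 95% interval, DE from ICC 0.02 |
|---|---|---|---|---|
| 40% | 330 | 5.0 | 34.7% to 45.3% | 34.5% to 45.5% |
| 50% | 264 | 4.0 | 44.0% to 56.0% | 43.8% to 56.2% |
| 60% | 220 | 3.3 | 53.5% to 66.5% | 53.4% to 66.6% |
| 70% | about 189 | 2.9 | 63.5% to 76.5% | 63.3% to 76.7% |

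Across this range the half-width stays between about 5.3 and 6.7 points, always below 8.5.

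**The case against.** The strongest reply is that nothing depends on the sentence. It is offered as an example of precision. The number of pharmacies and women comes from what the team thought it could recruit, not from this interval, and the threshold is applied as a bare percentage. The true precision is also better than stated. All of this stands, and it is why the point is minor.

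The replacement figures are not the article's own. The 264 women and 4 per pharmacy come from assuming exactly 50% participation, and the ICC of 0.02 is carried over to the decision to take part. In addition, women who decline at the pharmacy's first contact are never verified as eligible by the research team, so the eligible count is itself partly an estimate. This also stands: any restated interval should be labelled as an illustration under named assumptions. It does not rescue n = 132, which fits the stated definition at no participation rate short of 100%.

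A reader might infer three stronger things that the article does not support:
- **That only 66 women would be enrolled.** If 132 were the eligible number, a 50% rate would leave 33 per group and weaken the claim about detecting d ≥ 0.50. The Sample size section says plainly that 66 per group are to be recruited, so that reading is excluded and no power is lost.
- **That the final analysis will use the wrong denominator.** The Progression criteria section refers to eligible patients, the Outcomes section describes recruitment rates through eligible and enrolled patients, and the Analyses section reports such rates with 95% intervals. None of them divides by 132.
- **That the Wald calculation was done wrongly.** For p = 0.50 and n = 132 it reproduces, apart from the 0.1-point omission of the design effect. The fault is in the choice of n.

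**Conclusion.** The point holds as a minor error in a planning figure. The stated 41.5% to 58.5% is not the precision of the participation rate as the article defines it, because 132 is the expected number who agree. With 132 enrolled at the 50% threshold, the interval is about 44.0% to 56.0%, or 43.8% to 56.2% with the design effect. The half-width is about 6 points instead of 8.5. The omitted design effect accounts for 0.1 point of the stated figure.

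The error is conservative. It leaves the planned sample, the power statement, the progression threshold and the planned analysis as they are. The corrected figures rest on three assumptions: enrolment of 132, a participation rate of 50%, and an ICC of 0.02 with about 4 eligible women per pharmacy. The direction of the correction is the same at every rate from 40% to 70%.

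**What to change.** In the Sample size section, replace the participation example with one that names the expected number of eligible women as an assumption and uses it as n, with the design effect. For example:

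> Enrolling 132 women at a participation rate of 50% would require about 264 eligible women (about 330 at a 40% rate, about 189 at a 70% rate). With 264 eligible women, an assumed mean of 4 per pharmacy and an ICC of 0.02 (design effect 1.06), the Wald 95% CI around 50% is 43.8% to 56.2%.

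The team should substitute its own expected number of eligible women per pharmacy if it has one. The cost is one sentence. No new data, no change to the sample size and no change to the planned analysis are needed.

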### Analyses

Descriptive statistics for pharmacies, pharmacists, and patients in the PACHA program and UC group will be reported and compared. Acceptability and feasibility indicators such as recruitment and retention rates will be evaluated using percentages or means and 95% CI [69]. To explore preliminary effects on factors expected to influence AET adherence, generalized estimating equation (GEE) regression models will be used to compare patterns of change in scores of factors influencing AET adherence between the two groups over time. The group-by-time interaction *p*-value will be used to test the differences between the two groups. Effect sizes will be estimated using Cohen’s *d*. The required sample size for a large-scale cluster RCT will be estimated using the PDC, its variability, and ICC. Missing data will be handled using various strategies according to the variables. For instance, mean score imputation (if at least half of the items are completed) will be applied to scales, while listwise deletion will be used for other variables [70]. For qualitative data, thematic analysis of the interviews will be conducted [71, 72]. Since this is a pilot study, analyses will be performed at the end of the study, and no subgroup analyses will be performed.

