**Acceptability**							
Participation and retention rate	- Study data log	- Descriptive statistics		X	X	X	X
Uptake of program components	- Questionnaire - Website metrics	- Descriptive statistics		X	X	X	X
Satisfaction	- Questionnaire - Semi-structured interview	- Descriptive statistics - Thematic analysis			X	X	X
Perceived relevance, acceptability, and benefits	- Semi-structured interview	- Thematic analysis			X	X	X

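### The group-by-time test gains nothing from the baseline scores at the plan's own correlation, and the d ≥ 0.50 claim has almost no room for loss to follow-up

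*Protocol article*

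**What the plan says.** All places are in the protocol article.

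- **Analyses.** GEE regression models "will be used to compare patterns of change in scores of factors influencing AET adherence between the two groups over time". The p-value of the group-by-time interaction is the test, and effect sizes are reported as Cohen's d. Adjustment for the baseline score is not mentioned.
- **Table 3.** For intention, knowledge, attitude and the other factors measured twice, the metric is mean change. Scores are taken at baseline and at the end of the study only.
- **Data collection and management.** There are two questionnaires, one before randomization and one at 6 months. Non-responders are to be reminded by email and telephone.
- **Sample size.** The team expects to "recruit approximately 33 pharmacies and 66 patients per group". It then states: "The anticipated sample size will enable us to detect moderate to large effect sizes", meaning d of 0.50 or more. The inputs are a mean of 2 patients per cluster, an ICC of 0.02, a "correlation of 0.5 between baseline and 6-month follow-up", power 0.80 and α 0.05. No rate of loss to follow-up is given.
- **Table 3, Acceptability.** "Participation and retention rate" is listed as an outcome.
- **Progression criteria.** The program counts as promising on "an effect size of ≥ 0.50 on factors hypothesized to influence adherence".

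**The concern.** There are two linked points.

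First, the chosen test is inefficient on the plan's own inputs. With two time points and a separate baseline mean in each group, the group-by-time coefficient is exactly the between-group difference in mean change. A change score subtracts the whole baseline value, when a correlation of 0.5 justifies subtracting only half of it. The noise added by over-subtraction cancels the gain, so the baseline questionnaire contributes no precision to the comparison.

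Second, the detectable effect is calculated as if every recruited woman returns the 6-month questionnaire. The 66 per group is a recruitment figure, nobody can be added to a cluster after randomization, and the plan itself expects non-responders.

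At stake is the precision of the effect estimates that Progression criteria compares with 0.50. A noisier estimate is more likely to fall on the wrong side of that threshold by chance, in either direction.

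**Working it through.** **Inputs from Sample size:** 66 patients per group; mean cluster size 2; ICC 0.02; correlation r = 0.5; d = 0.50; power 0.80; α = 0.05. **Assumptions:** α is two-sided (not stated, but two-sided matches the planned 66); the ICC of 0.02 applies to the analysed score; loss is equal in the two groups. The document gives no loss rate, so a range is shown.

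**Step 1. Design effect.** 1 + (2 − 1) × 0.02 = 1.02. Effective n per group = 66 × retention / 1.02, which is 64.7 at full follow-up.

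**Step 2. Variance of the comparison, in units of the score's SD².**
- Change score (group-by-time): 2(1 − r) = 2 × 0.5 = 1.00
- 6-month score alone: 1.00
- 6-month score adjusted for baseline: 1 − r² = 1 − 0.25 = 0.75

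The ratio adjusted/change is (1 + r)/2 = 0.75, so the named test carries one third more variance. Since (1 + r)/2 is below 1 for every r below 1, the direction does not depend on r = 0.5.

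**Step 3. Reproduce the plan's figure.** By normal approximation, n per group = 2 × (1.960 + 0.842)² / 0.50² × 1.00 × 1.02 = 64.05, so 65 are needed against 66 planned. Detectable d at 66 is 0.493 (0.496 with the t distribution). The stated d ≥ 0.50 is therefore reproduced on the change-score basis with full follow-up. With baseline adjustment the same formula gives 64.05 × 0.75 = 48.04, so 49.

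**Step 4. Effect of loss** (two-sample t, effective n as in Step 1):

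| Loss | Change: detectable d | Change: power at 0.50 | Adjusted: detectable d | Adjusted: power at 0.50 |
|---|---|---|---|---|
| 0% | 0.496 | 81% | 0.430 | 90% |
| 2% | 0.501 | 80% | 0.434 | 90% |
| 5% | 0.509 | 79% | 0.441 | 89% |
| 10% | 0.524 | 76% | 0.453 | 87% |
| 15% | 0.539 | 74% | 0.467 | 85% |
| 20% | 0.556 | 71% | 0.482 | 83% |
| 25% | 0.575 | 68% | 0.498 | 80% |

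**Step 5. Loss at which power at d = 0.50 falls to 80%.**
- Change score: 1.5% (t) or 1 − 64.05/66 = 3.0% (normal), that is, one or two women per group.
- Baseline-adjusted: 26% (t) or 1 − 48.04/66 = 27% (normal).

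If clusters of 1, 2 and 3 are equally likely, the design effect is 1.027 and the normal-approximation limits become 2.3% and 26.7%.

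**Step 6. Sensitivity to the correlation** (power at d = 0.50, change score against adjusted):

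| r | 0% loss | 15% loss |
|---|---|---|
| 0.3 | 67% vs 84% | 59% vs 78% |
| 0.5 | 81% vs 90% | 74% vs 85% |
| 0.7 | 95% vs 98% | 92% vs 95% |

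**Step 7. Precision of the estimate read against 0.50.** The standard error of d is about √(2 × variance / effective n). At 15% loss the effective n is 55.0, giving √(2.0/55.0) = 0.191 for the change score and √(1.5/55.0) = 0.165 adjusted.

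**The case against.** The strongest reply is that nothing stated is wrong. A group-by-time GEE on randomized groups is a valid and common test, and the d ≥ 0.50 figure reproduces. That stands: this is a matter of efficiency and of a missing allowance, not of bias or faulty arithmetic.

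It can also be said that the article does not give the model's parameterization. In a longitudinal model with a common baseline mean, the treatment effect is also a group-by-time term and is already efficient. This is possible but not the natural reading, because Table 3 names mean change as the metric and Analyses speaks of comparing change.

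The decline is gradual, not a cliff. At 5% loss, power is still about 79% and detectable d is 0.51, for a sample described only as approximate. That is fair; the shortfall becomes material from about 10% to 15% loss, and those rates are assumptions.

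The gain also depends on r. The study's own scales have test–retest coefficients of at least 0.70, and if the 6-month correlation were that high, the change-score test would keep 80% power up to about 40% loss. But test–retest reliability does not establish the 6-month correlation, the plan chose 0.5, and a lower value makes the change score worse.

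Finally, the pilot is not designed for efficacy on adherence, its progression rule uses an effect size and not a p-value, and the plan works on retention through reminders and deferred training for control pharmacists. This limits the consequence. It does not remove it: Sample size still makes a power claim for these factors, and a tighter estimate serves an effect-size threshold as much as a test.

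**Conclusion.** The concern holds and should be acted on. The named test carries one third more variance than baseline adjustment at the plan's own correlation of 0.5. The stated d ≥ 0.50 at 80% power is correct only with near-complete follow-up, with slack of one or two women per group. At an assumed 15% loss the change-score test detects 0.54 (74% power at 0.50); the adjusted test detects 0.47 (85%).

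The sizes rest on a two-sided test, r = 0.5, an ICC of 0.02 for the analysed score, and the assumed loss rates. The size of the gain varies with r, but its direction does not. Importance is moderate, because these effects are exploratory, though they do feed a progression criterion.

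**What to change.** 1. **Analyses.** State that, for each factor measured at baseline and 6 months, the test is the group difference at 6 months adjusted for the baseline score, clustered on pharmacy. Either ANCOVA fitted by GEE or a longitudinal model with a common baseline mean will do. This replaces the unconstrained group-by-time term. Align the mean-change entries in Table 3.
2. **Cohen's d.** Say that the adjusted difference is divided by the SD of the score itself, not the residual SD. Dividing by the residual SD would turn a d of 0.50 into 0.50/√0.75 = 0.58 and change the meaning of the progression threshold.
3. **Sample size.** Give an assumed loss and restate the detectable effect after it: for example, at 15% loss, about 0.47 with baseline adjustment, or about 0.54 if the change-score test is kept.

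The cost is a sentence or two in Analyses and one restated figure. No new data, participants or visits are needed. Baseline is measured before randomization, so adjusting for it introduces no bias. If the change-score test is kept, the only cost is a slightly less favourable stated d.

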## Discussion

The goal of this pilot study is to assess the acceptability, feasibility of implementation, and preliminary effects of the PACHA program, a community pharmacy-based program designed to support patients prescribed AET for hormone-sensitive breast cancer. Following a mixed-methods design, multiple quantitative measures and indicators will be collected, along with qualitative semi-structured interviews conducted with participating patients and pharmacists.

In planning this pilot study, we anticipated several challenges and addressed them where possible. First, to prevent contamination of the intervention, we chose a cluster-RCT design. Such design implies that program training and tools are available exclusively to pharmacies randomized to the PACHA program group. However, since the training holds strong appeal for pharmacists, we decided to grant access to the training to those in the control group after the 6-month follow-up period. This decision will potentially have a positive effect on the control group retention rate. Second, while pharmacists and patients cannot be blinded to the intervention, the analyses will be performed in a blinded fashion. Third, evaluating such a complex, multifaceted intervention requires taking into account variables at the pharmacy, pharmacist, and patient levels. For this reason, we conceived our outcome assessment plan based on the Framework for the Implementation of Services in Pharmacy [26] and the Theory of Planned Behavior [50]. We also drew on our extensive program development and pre-testing phase [24, 32]. Finally, following the COVID-19 pandemic and based on feedback from community pharmacists, we decided to modify the delivery mode of our intervention, moving from in-person consultations to telephone consultations, and from mainly printed material to mostly web-based material [24]. Compared to in-person consultations, telephone consultations were deemed more flexible and feasible by our pharmacist informants. This approach is also more efficient in a context where patients do not always go to their community pharmacy to get their medication (e.g., most pharmacies offer medication delivery). We also consider that both the web-based training and resources are major assets of the PACHA program in the current post-COVID 19 context and could facilitate future dissemination and implementation of the program.

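### Nothing stated handles an unreturned 6-month questionnaire, so the effect size held against d ≥ 0.50 may be biased if dropout differs between arms

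*Protocol article*

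**What the plan says.** All references are to the protocol article.

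- **Measurement.** Data collection and management sets two questionnaires, one before randomisation and one at 6 months, with email and telephone reminders for non-responders.
- **Metric.** Table 3 lists mean change for intention, knowledge, attitude and the other factors in the conceptual model.
- **Model.** Analyses says "generalized estimating equation (GEE) regression models will be used to compare patterns of change in scores of factors influencing AET adherence", tested by the group-by-time interaction. No weighting for dropout is mentioned and no working correlation is named.
- **Effect size.** Analyses says "Effect sizes will be estimated using Cohen"'s *d*. It does not say whether *d* comes from the GEE fit or from observed changes.
- **Missing data.** "Missing data will be handled using various strategies according to the variables". Two examples follow. The first concerns gaps within a scale: "mean score imputation (if at least half of the items are completed) will be applied to scales". The second covers whatever is not a scale, and its rule is "listwise deletion will be used for other variables".
- **Use of the result.** Progression criteria counts "an effect size of ≥ 0.50 on factors hypothesized to influence adherence" as a sign that the program could improve adherence.

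**The concern.** With only two measurement times, a woman who does not return the 6-month form has no change score. Half-item imputation repairs gaps within a returned form and cannot create a score for one that was not returned. What happens to her in the estimate of *d* then depends on choices the article leaves open. Under the simplest readings, the estimate needs dropout to be completely at random or to act the same way in both arms.

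Differential dropout is plausible. Patients know their group and the outcomes are self-reported. The article also treats control-group retention as worth protecting: on offering training to control pharmacists after follow-up, the Discussion says "This decision will potentially have a positive effect on the control group retention rate".

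At stake is a numerical progression indicator. Selective loss could move *d* towards or across 0.50 for reasons unrelated to the program. The baseline scores that would correct for baseline-dependent loss are available, because clusters are randomised only after the baseline questionnaires are completed.

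**Working it through.** **1. The plan's own figure.** Inputs from Sample size: 66 patients per group, mean cluster size 2, ICC 0.02, baseline to 6-month correlation *r* = 0.5, power 0.80, α = 0.05 (taken as two-sided).
- Design effect = 1 + (2 − 1) × 0.02 = 1.02. Effective n = 66 / 1.02 = 64.7 per arm.
- SD of change = √(2 × (1 − 0.5)) = 1 baseline SD, so a shift in SD units is also a shift in *d*.
- Detectable *d* = (1.96 + 0.842) × √(2 / 64.7) = 0.49, and power at *d* = 0.50 is 0.81. The stated 0.50 reproduces with no dropout.
- Standard error of the difference in change = √(2 × 1.02 / 66) = 0.18.

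**2. Bias formulas.** Let m_I and m_C be the mean baseline score, in SD units from the randomised mean, of women who return the 6-month form in the program and control arms. When dropout depends on baseline only:
- completers' mean change: bias = (r − 1)(m_I − m_C);
- GEE on all records with independence working correlation: bias = r(m_I − m_C).

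At *r* = 0.5 the two are equal in size and opposite in sign. Both are zero when m_I = m_C.

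**3. Assumed scenarios.** The protocol gives no dropout rate, so every rate and mechanism below is an assumption. The means come from integrating a logistic dropout model over a standard normal baseline.

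| Scenario | m_I − m_C | Completers' change | Independence GEE |
|---|---|---|---|
| 10% control, 20% program; log-odds of dropout +1 per SD lower baseline in both arms | +0.082 | −0.04 | +0.04 |
| (a) 20% control, odds doubled per SD lower baseline; 10% program, random | −0.129 | +0.06 | −0.06 |
| 10% control, 30% program; same mechanism as the first row | +0.162 | −0.08 | +0.08 |
| (b) 25% per arm, opposite selection, odds ratios 3 and 2 per SD | −0.387 | +0.19 | −0.19 |
| (c) 30% per arm, opposite selection, odds ratio 3 per SD | −0.540 | +0.27 | −0.27 |

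Equal selective dropout (20% per arm, same mechanism) gave no bias with any of these estimators.

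**4. Other working correlations, true effect 0.** In (a), GEE exchangeable within pharmacy gave about −0.05, and a model with the correct patient-within-pharmacy correlation gave 0.00. GEE exchangeable within patient gave −0.002, −0.013 and −0.022 in (a), (b) and (c).

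**5. Against the threshold, true d = 0.40.** In (a), completers' change gives 0.40 + 0.06 = 0.46 and independence GEE 0.40 − 0.06 = 0.34. In (b) they give 0.40 + 0.19 = 0.59 and 0.40 − 0.19 = 0.21.

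**6. Dropout that depends on the 6-month score itself.** With true *d* = 0.40 and 10% control, 30% program dropout, completers' change, independence GEE and patient-level exchangeable GEE gave 0.48, 0.56 and 0.52.

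**The case against.** The case against has real weight.

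- **Listwise deletion.** A reader might infer that it is applied to the 6-month scale scores. The sentence assigns it to variables other than scales, and both rules are given as examples. This stands.
- **Who is analysed.** A reader might also infer that GEE keeps only women who return the 6-month form. It does not. In a simulated sample of 132 women with about 20% of 6-month records missing, GEE on all records kept all 132 (240 records), while listwise deletion kept 108 (216 records).
- **Working correlation.** GEE exchangeable within patient fits the text equally well and leaves almost no bias when dropout depends on baseline only. This stands. However, the article does not choose that structure, and Table 3's mean change points towards completers if *d* is taken from it.
- **Likelihood of differential dropout.** The training offer is a mitigation aimed at pharmacists, control patients get website access at the end, and reminders are sent. None of this shows that selective patient dropout will occur. It is plausible, no more.
- **Size.** Scenarios (b) and (c) need heavy loss with opposite selection in the two arms, which nothing in the protocol suggests. The 0.06 SD in (a) is about a third of the 0.18 standard error.
- **Scope.** This is a condensed article about a pilot that says it is not designed to test efficacy on adherence, and fuller detail may sit elsewhere. That limits the weight of the point. It does not remove it, because the article itself fixes the model, the metric, the imputation rule and a numerical threshold, and these together do not address an unreturned form.

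**Conclusion.** The point holds in limited form. No stated method covers an unreturned 6-month questionnaire. Under completers' mean change, or GEE with independence or pharmacy-level exchangeable correlation, the *d* compared with 0.50 relies on dropout being completely at random or acting alike in both arms.

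Under assumed baseline-dependent dropout that differs by arm, with *r* = 0.5, the bias is about 0.04 to 0.06 SD in moderate scenarios, 0.08 SD at 10% against 30% loss, and about 0.2 to 0.27 SD in extreme ones. Its direction depends on the estimator. These are conditional ranges and not a forecast, since the protocol gives no dropout figure.

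The documents do not support saying that the scale analyses drop every woman without a 6-month form, that selective dropout is likely, or that the result will be biased by a particular amount. The analysis is exploratory, so the consequence is modest, but it feeds a stated progression indicator and the remedy is nearly free.

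**What to change.** Estimate the group-by-time effect, and derive *d*, from a linear mixed model fitted by REML. Give it random effects for pharmacy and for patient within pharmacy, and use all available baseline and 6-month scores of every randomised woman. Multiple imputation by arm using the baseline scores is an acceptable alternative. Say explicitly that *d* comes from this model. Keep half-item imputation for item gaps within returned questionnaires only. Show the GEE or completers' result as a sensitivity analysis, with its working correlation named.

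The cost is a few lines of analysis-plan text and slightly more programming, with no new data. The change does not remove bias from dropout that depends on the unseen 6-month score, so *d* should be read alongside 6-month retention by arm, which the study already collects.
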